### Quality control

The clinical research unit will satisfy the requisite clinical research conditions for drug research, as determined by the National Medical Products Administration of China. Investigators will be clinically trained physicians who work under the direction of a senior physician. Clinical wards will be standardized to ensure that rescue equipment is fully functional. Medications will be administered by professional caregivers, and patient compliance will be ensured by learning about the medication. The standard operating rules of clinical trials will be followed and implemented in the research center. All clinical procedures will be supervised, and the complete and correct reporting of all data will be confirmed by comparing case report forms and the source data. In the event that an SAE occurs, it will be promptly reported to each research unit and, if necessary, the trial will be temporarily discontinued.

### Ethics and dissemination

#### Ethics and informed consent

The trial will be conducted in accordance with Good Clinical Practice guidelines, the guiding principles of the Declaration of Helsinki, and applicable local laws and regulations. The study protocol was approved by the IEC of the Liaoning Provincial Cancer Hospital in October 17, 2018 (approval No. 20180948–2) (Additional file 2) and the trial has been registered at ClinicalTrials.gov (identifier: NCT03932526). This research plan refers to protocol V2.0.

Written informed consent will be given by each patient prior to participation in the trial. The investigator will inform the patients that participation in the study is voluntary, and that they can withdraw at any time. Patients will be informed that the investigator will maintain their records over the long-term follow-up period, and that their records may be viewed by relevant management officers, within the limits of relevant laws and regulations. The privacy of all patients will be protected.

#### Dissemination

The final research results will be disseminated through publications in peer-reviewed academic journals and at international academic conferences.

### Protocol amendments

All amendments to the protocol will be signed and dated by the Department of Breast Medicine, the Liaoning Provincial Cancer Hospital, China, and approved by the IEC before release. Any protocol deviation that may occur during the study will be promptly managed by the investigator. The protocol deviation, including reason(s) for its occurrence, will be documented in the case report form and the original case report, which will be retained in the research unit by the Sponsor.

### Principle of confidentiality

Collection and use of patient data will comply with relevant laws and regulations that protect the subjects’ privacy, and full confidentiality will be maintained. The participants have the right to obtain their personal data through the investigator, and to modify any errors or incomplete data. No personal information will be disclosed to unauthorized parties. The Sponsor will maintain the confidentiality of all personal data throughout the study period.

### Compensation

The drugs used in this trial will be provided by the pharmaceutical company; the company has no role in the study design; collection, management, analysis, and interpretation of data; writing of the report; or the decision to submit the report for publication.

Each patient having provincial, municipal, remote, or new rural cooperation medical insurance will be subsidized with RMB 600 yuan (~ 85.5 USD) after completing one chemotherapy cycle. Self-paying patients will be given the subsequent cycle of chemotherapy free of charge (chemotherapy drugs only) after the initial cycle of chemotherapy.

Compensation mechanism: the specific compensation standards and methods will be clarified before the trial, and the Sponsor will provide clinical trial insurance for each subject. Treatment costs for drug-related adverse events and corresponding economic compensation will be undertaken by the Sponsor.

## Discussion

The anti-tumor effect of conventional chemotherapy relies on a single maximum tolerated dose. Despite its wide use, traditional scheduling of chemotherapy cycles is not convenient for patients, as frequent hospital visits for infusion and in-patient admission are required. To reduce the side effects of chemotherapy, treatment cycles are separated by longer intervals. This prospective randomized controlled trial, conducted in Liaoning Province of Northeast China, will be the first to analyze the efficacy of apatinib-targeted therapy, combined with vinorelbine chemotherapy, in treating patients with recurrent or metastatic TNBC, who have previously received anthracyclines and taxanes. Some limitations should be acknowledged in the current study protocol. As all subjects are limited to the northern Chinese population, the study results may not be generalizable to other patient populations. Furthermore, the sample size is relatively small, and this is due to limitations in staffing and funding.

Based on the data from this trial, we hope to identify an optimal treatment regimen that is suitable for female patients with TNBC in Northeast China, who have been treated with anthracyclines and taxanes.

### Trial status

The trial was registered at ClinicalTrials.gov (identifier: NCT03932526) on 30 April 2019. Patient recruitment will begin in June 2019, and end in August 2022. Analysis of the primary outcome measure will be completed in December 2022. The study will end in June 2023. This research plan refers to protocol V2.0.

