### Sample size

The survival time of the patients will be compared between the two groups by the log-rank test, using PASS Sample Size Software 11.0 (NCSS LLC, Kaysville, Utah, USA) [35]. Based on previous experience [36] and pilot study results, the mPFS was estimated to be 4.1 months in the vinorelbine monotherapy group and 6.7 months in the vinorelbine plus apatinib group (hazard ratio (HR) = 0.61). The recruitment time is expected to be 26 months (from the beginning of recruitment to the enrollment of the last patient) and a 15-month follow-up time is planned. Assuming a dropout rate of 10% across both groups, power of 80%, and two-sided significance of α = 0.05, a sample size of 238 patients (119 in each intervention group) will be required.

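### The sample-size section and the trial calendar give different timing: 26 + 15 months against 38 + 4, with a small effect on PFS power if the printed dates are real

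*Protocol article*

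**What the plan says.** The Sample size section of the protocol article gives two timing inputs for the log-rank calculation. On recruitment: "The recruitment time is expected to be 26 months (from the beginning of recruitment to the enrollment of the last patient". On follow-up: "a 15-month follow-up time is planned". Together these make 41 months.

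The Trial status section gives the calendar. On recruitment: "Patient recruitment will begin in June 2019, and end in August 2022". On the primary analysis: "Analysis of the primary outcome measure will be completed in December 2022". On closure: "The study will end in June 2023".

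The Statistical analysis section plans no interim analysis. The article gives no event count that would trigger the primary analysis, so the December 2022 date is the only timing stated for it.

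**The concern.** Recruitment length and follow-up are inputs to the sample size, because they fix the expected proportion of patients with a PFS event. The article defines the recruitment period as running from its start to the last enrolment, so 26 months cannot be read as 38. On the printed dates recruitment is 12 months longer than assumed, and the interval from the last patient to the primary analysis is 11 months shorter.

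Two things are at stake. The first is whether 238 patients still give the stated 80% power. The second is which schedule the trial will follow. For late entrants, a minimum follow-up of at most 4 months is slightly below the assumed control median PFS of 4.1 months.

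**Working it through.** **Dates**

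| Interval | Sample size section | Trial status section |
|---|---|---|
| Start to last patient | 26 months | June 2019 to August 2022 = 38 months (39 if both end months count in full) |
| Last patient to primary analysis | 15 months | August to December 2022 = at most 4 months |
| Last patient to study end | not given | August 2022 to June 2023 = 10 months |
| Start to primary analysis | 26 + 15 = 41 months | 38 + 4 = 42 months |

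The 15 months is taken to run from the last enrolment. June 2019 + 26 months = August 2021, and 15 more months gives November 2022, just before the December 2022 analysis.

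**Inputs (Sample size section):** "the mPFS was estimated to be 4.1 months in the vinorelbine monotherapy group and 6.7 months in the vinorelbine plus apatinib group"; two-sided α 0.05; power 80%; 10% dropout with no time unit; 119 per arm.

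**Assumptions:** exponential PFS, uniform recruitment over R months, minimum follow-up F months, loss hazard η.

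**Formulas**
- Hazards: λ = ln 2 / median, so 0.1691 (control) and 0.1035 (combination) per month. The hazard ratio is 4.1/6.7 = 0.612 and |ln HR| = 0.491.
- Event probability: p = λ/(λ+η) × [1 − (e^(−(λ+η)F) − e^(−(λ+η)(R+F))) / ((λ+η)R)].
- Events needed (Schoenfeld): 4 × (1.96 + 0.84)² / 0.491², about 131.
- Power: Φ(√(D/4) × 0.491 − 1.96), with D the expected events.

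**Reproducing 238.** With 10% lost per month (η = −ln 0.9 = 0.1054) and 26 + 15, p is 0.615 and 0.491, mean 0.553, and 131/0.553 is about 237. A stepwise log-rank calculation of the Lakatos type gives 237.7, hence 238. With 10% as overall dropout, mean p is 0.954, so 131/0.954 = 137.3, and 138/0.9 rounds up to 154 (159 with Freedman's 136 events). So the monthly reading reproduces 238 and the overall reading does not. The monthly unit is an assumption.

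**Printed dates against plan, PFS**

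| Reading of the 10% | Schedule | p control / combination | Events | Power |
|---|---|---|---|---|
| Overall (238 × 0.9 = 214 evaluable) | 26 + 15 | 0.982 / 0.927 | 204 | 94% |
| Overall | 38 + 4 | 0.921 / 0.835 | 188 | 92% |
| Per month (N = 238) | 26 + 15 | 0.615 / 0.491 | 132 | 80.4% |
| Per month | 38 + 4 | 0.596 / 0.468 | 127 | 78.9% |

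For the last row: 119 × (0.596 + 0.468) = 126.7 events, and Φ(√(126.7/4) × 0.491 − 1.96) = 0.789. Under the monthly reading the required N is about 247 for 38 + 4 and about 239 for 38 + 10.

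**OS.** The article states no OS assumption for this trial, so the medians below are borrowed from other regimens in its Table 1 for illustration, without dropout.

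| Median OS | 26 + 15 | 38 + 4 (December 2022) | 38 + 10 (June 2023) |
|---|---|---|---|
| 10.6 months | 82% | 72% | 81% |
| 18.9 months | 63% | 53% | 63% |

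**The case against.** The strongest reply is that this is a typing error in one year. The two totals differ by one month, and August 2021 makes every other date fit. If so, no follow-up is lost and no calculation changes. That is the likeliest explanation, but the article cannot confirm it, and the text as printed still gives two incompatible schedules. A reader might infer from the dates that the planned follow-up will definitely not be delivered. That treats the printed year as established, and it is not.

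The second reply is that PFS hardly depends on the split between recruitment and follow-up, because the medians are short and most patients enter early. This stands. By December 2022 about 27/38 = 71% of uniformly recruited patients would have at least 15 months of potential follow-up even on the printed dates. A reader might also infer that the most recent entrants would contribute mainly censored times. Averaged over the arms and without dropout, the event probability reaches 50% at about 5.2 months. With a 4-month minimum, only those entering in about the last 1.2 months of recruitment (1.2/38 = 3%, some 7 of 238) are more likely censored than not.

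The third reply concerns OS. The Trial status section assigns only the primary outcome to December 2022, and the Follow up section tracks survival until death or study completion. The article does not say that OS will be read in December 2022, so a claim that OS will be immature is not supported.

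**Conclusion.** The contradiction is real and stands as written: 26 against 38 months of recruitment, and 15 against at most 4 months from the last patient to the primary analysis (10 to study end). It concerns inputs on which the sample size rests. Which section is wrong cannot be settled from the article.

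The consequence for PFS is small if the printed dates are meant, about 1.5 to 2 points of power. With 10% overall dropout, power stays far above 80%. With 10% monthly loss, the reading that reproduces 238, it falls just under the stated 80%, to 78.9%. A reader might infer a materially underpowered trial, but the article's figures do not support that. OS event fractions would be about 10 points lower only if OS were read in December 2022. At June 2023 they are essentially as planned.

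These sizes rest on exponential survival, uniform recruitment and the stated medians. The date conflict rests on none of them.

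**What to change.** Reconcile the two sections in one of two ways.

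- If 26 + 15 months is the plan, correct the end of recruitment in the Trial status section to August 2021. This changes one date and no calculation.
- If August 2022 is intended, replace 26 + 15 in the Sample size section with the actual periods: 38 + 4, or 38 + 10 if the primary cut-off is moved to study end. Then restate the power for 238 patients, giving the time unit of the 10% dropout used. This costs one rerun of the calculation and a sentence of text.

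Moving the primary analysis to 15 months after an August 2022 last enrolment (November 2023), or tying it to an event count, would also remove the conflict. Both are optional, because neither is needed to resolve the contradiction and the PFS power does not call for them.

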## Data Availability

The results of this study will be disseminated via peer-reviewed publications and conference presentations. No data are available at the moment.

## Abbreviations

AJCC: American Joint Committee on Cancer
ALT: Alanine aminotransferase
ANC: Absolute neutrophil count
AST: Aspartate aminotransferase
CEA: Carcinoembryonic antigen
CI: Confidence interval
CR: Complete response
CT: Computed tomography
DCR: Disease control rate
DILI: Drug-induced liver injury
DRQ: Data request queue
ECOG: Eastern Cooperative Oncology Group
ECOG-PS: Eastern Cooperative Oncology Group performance status
EDC: Electronic data capture system
EORTC QLQ-C30, version 3: European Organization for Research and Treatment of Cancer Quality of Life Questionnaire Core-30
ER: Estrogen receptors
HER-2: Human epidermal growth factor receptor 2
IDMB: Independent Data Monitoring Board
IEC: Independent Ethics Committee
mOS: Mean overall survival
mPFS: Mean progression-free survival
MRI: Magnetic resonance imaging
mTTP: Median time to progression
NCI-CTC: National Cancer Institute Common Toxicity Criteria
ORR: Objective response rate
OS: Overall survival
PR: Progesterone receptors
RECIST: Response Evaluation Criteria in Solid Tumors
SAEs: Serious adverse events
SPIRIT: Standard Protocol Items - Recommendations for Interventional Trials
TNBC: Triple-negative breast cancer
TTP: Time to progression
ULN: Upper limit of normal
VEGF: Vascular endothelial growth factor
VEGFR: Vascular endothelial growth factor receptor
